## Abstract

**Background:**

Cancer chemotherapy is frequently associated with a decline in general physical condition, exercise tolerance, and muscle strength and with an increase in fatigue. While accumulating evidence suggests that physical activity and exercise interventions during chemotherapy treatment may contribute to maintaining cardiorespiratory fitness and strength, the results of studies conducted to date have not been consistent. Additional research is needed to determine the optimal intensity of exercise training programs in general and in particular the relative effectiveness of supervised, outpatient (hospital- or physical therapy practice-based) versus home-based programs.

**Methods:**

This multicenter, prospective, randomized trial will evaluate the effectiveness of a low to moderate intensity, home-based, self-management physical activity program, and a high intensity, structured, supervised exercise program, in maintaining or enhancing physical fitness (cardiorespiratory fitness and muscle strength), in minimizing fatigue and in enhancing the health-related quality of life (HRQoL). Patients receiving adjuvant chemotherapy for breast or colon cancer (n = 360) are being recruited from twelve hospitals in the Netherlands, and randomly allocated to one of the two treatment groups or to a 'usual care' control group. Performance-based and self-reported outcomes are assessed at baseline, at the end of chemotherapy and at six month follow-up.

**Discussion:**

This large, multicenter, randomized clinical trial will provide additional empirical evidence regarding the effectiveness of physical exercise during adjuvant chemotherapy in enhancing physical fitness, minimizing fatigue, and maintaining or enhancing patients' quality of life. If demonstrated to be effective, exercise intervention programs will be a welcome addition to the standard program of care offered to patients with cancer receiving chemotherapy.

**Trial registration:**

This study is registered at the Netherlands Trial Register (NTR 2159)

## Background

Treatment with chemotherapy is associated with multiple physical and psychosocial side effects, including reduced cardiorespiratory fitness and muscle strength and increased fatigue [1,2]. Fatigue is a common problem reported by patients undergoing chemotherapy, with prevalence rates ranging from 80% to 100% [3-5]. Among breast cancer survivors, the prevalence of chronic, severe fatigue has been reported to range from 24% to 40%. Chronic fatigue has a negative impact on activities of daily life, social reintegration and overall quality of life [3]. Fatigue and muscle wasting may be directly therapy-induced, but may also be attributed in part to sedentary habits and subsequent loss of physical fitness (cardiorespiratory fitness and muscle strength) [6].

There is accumulating evidence that exercise interventions during chemotherapy may contribute to preserving cardiorespiratory fitness [7-14] and muscle strength [13,15,16], decreasing fatigue [13,14,17-19], mood disturbances [13,14,17,18] and lean body mass [13], and enhancing self-reported functioning [18], overall HRQoL [13,14,18] and immune-function [17].

However, results of studies to date have not been entirely consistent [17,18,20], which may be due, in part, to methodological limitations. Most studies have employed small sample sizes (ranging from 6 to 60 patients in the intervention arm) and some have failed to include a control group. Furthermore, the interventions employed in these studies varied widely. Some studies have investigated low intensity, home-based exercise programs, while others report on intensive, structured and supervised training, with or without resistance training [14]. Most of the previous studies employed exercise programs that are less than optimal in terms of important aspects of exercise physiology [17]. It is hypothesized that an intervention that combines resistance training and aerobic exercise may be most effective [15].

Adherence to exercise interventions is a challenging task [20]. When shaping an exercise program to the needs of the individual patient, current fitness level, health beliefs and health behavior need to be taken into consideration, while still maintaining a core, standardized program that can be relatively easily implemented in a range of health care settings [20].

Effects of exercise interventions may be moderated by exercise history and health beliefs. It is likely that sociodemographic, medical variables, and patients' preferences also moderate the effects of exercise interventions during chemotherapy [21,22].

It should be noted that most trials are characterized by low participation rates (as low as 17% of potentially eligible patients), which may limit the generalizability of the results, particularly if those included in the trial tended to be more habitually active, more highly motivated and/or better educated than the target population as a whole [13,14].

Finally, to our knowledge, no study to date, has evaluated the cost-effectiveness of exercise interventions during chemotherapy.

In summary, while there is evidence supporting the beneficial effects of exercise programs during chemotherapy, the results across studies are not entirely consistent. Additional studies are needed to determine the optimal content, intensity, and form of exercise training programs. Specifically, there is need for research that investigates an exercise program that combines aerobic exercise and muscle strength training, as well as the relative effectiveness of supervised, outpatient versus unsupervised home-based programs. Such research should also consider the possible moderating effect of exercise history, current levels of fitness and physical activity, health attitudes, and motivation on physical exercise program effectiveness. The sample size and thus power of future trials should be sufficient to be able to demonstrate program effectiveness and cost-effectiveness based on both physiological performance measures, and fatigue.

In this article, we describe the design of a randomized, controlled, multicenter clinical trial comparing: (1) a low to moderate intensity, home-based, self-management physical activity program (Onco-Move), (2) a high intensity, structured, supervised exercise program (OnTrack) and (3) usual care control group, in patients undergoing adjuvant chemotherapy for breast or colon cancer.

We hypothesize that patients who undergo the Onco-Move or the OnTrack program will achieve better physical fitness levels, as assessed by objective performance tests, will report less fatigue, less mood disturbance, higher levels of physical activity and functioning in daily life, and better HRQoL than patients in the usual care control group. Furthermore, we hypothesize that patients in the OnTrack program will achieve more muscle strength and achieve greater gains in cardiorespiratory fitness than patients who follow the Onco-Move program. No differences are expected between the two programs in self-reported outcomes during treatment. However, it is hypothesized that, at the six month follow-up, patients who participated in the OnTrack program will report less fatigue, and higher levels of physical activity and functioning than those who participated in the Onco-Move program or usual care control group. Finally, we hypothesize that the OnTrack and Onco-Move programs will lead to a reduction in health care costs, patient and family costs, and costs of production losses, resulting in an cost-effective intervention.

If demonstrated to be effective, the availability of such physical activity and exercise intervention programs will be a welcome addition to the standard program of care offered to patients with cancer undergoing chemotherapy.

## Methods

The present trial is one of four randomized controlled trials included in the Alpe d'HuZes Cancer Rehabilitation (A-CaRe) program. All studies within the A-CaRe program will evaluate the effectiveness and the cost-effectiveness of exercise-based rehabilitation interventions in different cancer patient and survivor groups. In the PACES study, patients are being randomized to one of three study arms. They will participate either in the Onco-Move or the OnTrack program, or will undergo usual care. The design of the trial and the anticipated flow of the participants are displayed graphically in Figure 1. The trial has been approved by the institutional review board of the Netherlands Cancer Institute (under number PTC 09.2711), as well as by the review boards of all hospitals from which patients are being recruited. This protocol follows the CONSORT guidelines [23]. Patient recruitment and data collection for this trial started in April, 2010.

**Figure 1 F1:**
[figure not shown]
**Overview of study procedures**.

### Study sample

The study sample will be composed of patients with histologically confirmed primary breast or colon cancer who are scheduled to undergo adjuvant chemotherapy. There is no upper age limit for study participation.

Potentially eligible patients are screened for the presence of comorbid conditions that would contraindicate participation in a physical activity/exercise program. This includes patients with serious orthopedic conditions that would hamper functional recovery, and patients with serious cardiovascular or cardiopulmonary conditions (or risks) who would not be able to train at the intensity level required. Patients suffering from malnutrition as evidenced by a BMI < 18 kg/m^2^, unintended weight loss of more than 5% per month, or more than 10% unintended weight loss during the previous six month period are considered poor candidates for physical condition training and thus are not eligible for participation. Patients judged to have serious psychiatric or cognitive problems that would preclude them from program participation are excluded from the study. For assessment purposes, study participants need to have basic fluency in the Dutch language. Finally, patients participating in concurrent studies or rehabilitation programs containing elements of physical activity or exercise are also ineligible for the study.

### Recruitment and randomization

In total 360 patients are being recruited from twelve community or university hospitals in the wider Amsterdam region of the Netherlands. All potentially eligible patients are identified by their medical oncologist or nurse practitioner, and receive written information about the trial. The patients are contacted by telephone to provide additional information about the trial and to confirm their eligibility. If the patient chooses to participate in the trial, (s)he is invited for an intake session where written informed consent is obtained and baseline assessments are made. Subsequently, patients are assigned to one of the three study groups by means of the minimization method [24], which is balanced on age, primary diagnosis, treating hospital and the use of trastuzumab.

Patients who decline to participate in the trial are asked to complete a one-time questionnaire assessing basic sociodemographic, attitudinal, and behavioral data, and to determine the reason(s) for non-participation.

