### Power calculation

The primary study outcomes include two performance measures (cardiorespiratory fitness and muscle strength) and self-reported fatigue. It is expected that patients in the usual care condition will experience a 5%-10% decline in physical fitness during their chemotherapy treatment, that this will improve gradually during the post-treatment period, but will not necessarily return to pretreatment levels. It is hypothesized that the OnTrack program will yield at least a 20% improvement in general physical fitness. Based on the results of Courneya et al., a pretreatment mean for the 1-repetition maximum for leg extension is estimated to be 25 kg, with a standard deviation of 12 kg [15]. We expect that the Onco-Move program will help patients to maintain their pretreatment levels of cardiorespiratory fitness, but not necessarily improve, and that it will have little or no effect on muscle strength.

Based on the above figures, 100 patients per group are needed to detect a 0.40 standard deviation difference (Cohen's effect size [47]) in performance-based outcomes between the OnTrack group and the usual care group at the post-chemotherapy assessment, with power set at 0.80 and alpha at 0.05 (two-sided test).

We will recruit 360 patients into the trial to allow for an attrition of approximately 20% (i.e., patients who discontinue participation in the trial entirely, including failure to complete follow-up assessments). These numbers will be sufficient to detect a one-half standard deviation unit difference in self-reported fatigue. This magnitude of difference is generally considered to be indicative of clinically meaningful differences in patients' self-reported symptom experience [47,48].

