### Statistical analyses

All primary statistical analyses will be conducted on an intention-to-treat basis. Between group differences over time in performance indicators of general physical condition and muscle strength will be evaluated using multilevel regression analysis for % change from baseline, and two factor (group × time) multivariate analysis of variance with repeated measures on the time factor for comparison of mean scores. Scores on the self-report measures of fatigue, mood state and HRQoL will be calculated according to published scoring algorithms. Between-group differences over time in mean scores will be tested using a two factor (group × time) multivariate analysis of variance with repeated measures on the time factor. Effect sizes will be calculated using standard statistical procedures.

Supplementary analyses will be carried out in which data relating to compliance with the program elements are taken into account. Specifically, we will determine whether the level of compliance (based on attendance records and self-report data) is associated significantly with the changes over time in physical condition, muscle strength, fatigue, mood, and HRQoL. Similarly, we will investigate whether program effectiveness varies significantly as a function of patients' background characteristics, and particularly those variables assessing life style, health behavior and health attitudes.

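### The four minimisation factors are not named in the stated between-group models; to the extent that they predict the analysed response, standard errors are too wide and some precision is forgone.

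*Protocol article*

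**What the plan says.** Under Recruitment and randomization, the article says that "360 patients are being recruited from twelve community or university hospitals" and that assignment to the three groups uses the "minimization method [24], which is balanced on age, primary diagnosis, treating hospital and the use of trastuzumab".

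Under Statistical analyses, two models are named.

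- For the self-report measures of fatigue, mood and quality of life: "Between-group differences over time in mean scores will be tested using a two factor" design with group and time as the factors. Mean scores on the performance measures get the same "two factor (group × time) multivariate analysis of variance with repeated measures on the time factor".
- For the performance measures there is also a "multilevel regression analysis for % change from baseline". Its levels and covariates are not given.

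Patient characteristics appear in that section only as a supplementary question about effect modification: "we will investigate whether program effectiveness varies significantly as a function of patients' background characteristics". That is not adjustment of the main comparison.

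The Power calculation section says that "100 patients per group are needed to detect a 0.40 standard deviation difference" between OnTrack and usual care after chemotherapy, at 80% power and a two-sided 5% level.

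**The concern.** Minimisation makes the arms alike on the chosen factors. The part of the outcome variance that those factors explain then contributes little to the chance difference between arms. A model without the factors still counts that part as error, so its standard error is larger than the real sampling variation under the allocation used. Confidence intervals are then wider than they need be, p-values too large, and the precision gained through balanced allocation goes unused.

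The article gives some reason to think that the factors matter:

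- Background expects sociodemographic and medical variables to moderate exercise effects.
- Usual care says that control treatment varies with hospital guidelines.
- The OnTrack section describes a modified upper-body programme for breast cancer patients after axillary dissection, which ties diagnosis to strength training.

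None of this is quantified.

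**Working it through.** **Inputs from the protocol article.** Four minimisation factors, one of them hospital with 12 levels; 360 patients in three arms; difference 0.40 SD; 100 per group; two-sided 5% level; power 80%.

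**Assumed input.** R², the share of the variance of the analysed response that the four factors explain. The documents give no value, so a range is shown. The difference of 0.40 SD is taken on the scale of the analysed response.

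**Step 1: the plan's own figure.** n per group = 2(1.960 + 0.842)² / 0.40² = 98.1, so 99 by the normal approximation. The t-test version gives 99.1, so 100. Power at 100 per group is 80.7%. The stated 100 is reproduced.

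**Step 2: effect of leaving the factors out, with full balance.** With the total SD set to 1 and n = 100 per group:

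- standard error used by the unadjusted model: √(2/n) = 0.1414
- true standard error: √(1 − R²) × √(2/n)
- overstatement: 1/√(1 − R²)
- true type I error: 2[1 − Φ(1.96/√(1 − R²))]
- unadjusted power: Φ[(0.40 − 1.96 × 0.1414) / true SE]
- adjusted power: Φ[0.40 / true SE − 1.96]

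Example, R² = 0.20: true SE = 0.8944 × 0.1414 = 0.1265. Unadjusted power = Φ(0.1228/0.1265) = Φ(0.971) = 83.4%. Adjusted power = Φ(3.162 − 1.960) = Φ(1.202) = 88.5%.

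| R² (assumed) | SE too wide by | True type I error | Power unadjusted | Power adjusted | Forgone (points) |
|---|---|---|---|---|---|
| 0 | 0% | 5.0% | 80.7% | 80.7% | 0 |
| 0.05 | 2.6% | 4.4% | 81.4% | 82.7% | 1.3 |
| 0.10 | 5.4% | 3.9% | 82.0% | 84.6% | 2.6 |
| 0.20 | 11.8% | 2.8% | 83.4% | 88.5% | 5.1 |

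**Step 3: simulation of the allocation.** Three-arm minimisation of 300 patients over 12 hospitals and three binary factors, with 1,500 runs per scenario. Factor frequencies, effects and within-patient correlation were assumed.

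- Single post-treatment score, R² = 0.20: the unadjusted model SE was 0.141 against an empirical SE of 0.125 to 0.128. Without a true effect, 3.1% of unadjusted tests rejected. At 0.40 SD, power was 83.9% unadjusted and 88.7% adjusted. This agrees with Step 2.
- R² = 0.05: the null rejection rate was 4.9%. The Monte Carlo error is √(0.05 × 0.95/1500) = 0.6 points, so the simulation cannot separate this from the formula's 4.4%.
- Change from baseline, R² = 0.20 for level, factors with no effect on change: power was 94.3% unadjusted and 93.9% adjusted. Adjustment gains nothing here.

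**Step 4: which contrast the plan tests.** The group × time test is a within-patient contrast. A factor that raises or lowers a patient's scores equally at all visits cancels out of it. For that test, R² in the table must be read as the share of variance in *change*. For a comparison of post-treatment scores, which is how the power calculation is framed, effects on level count too.

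**The case against.** The strongest objection is that this is a condensed article. Naming group and time as design factors need not exclude covariates, and a covariate list is commonly left to an analysis plan that is not shown here. That stands in part: the documents do not show that the final analysis will be unadjusted. But the article is not silent about the model. It names one by its factors, and as named it does not reflect the allocation. If the analysis plan already adds the four factors, one sentence in agreement with it settles the point.

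Second, the multilevel regression covers performance outcomes and may carry hospital as a level. That is possible but not stated. It is not named for fatigue, which is also a primary outcome, and a hospital level would still leave out age, diagnosis and trastuzumab.

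Third, the loss may be nil. This stands. For the group × time test a loss arises only if the factors predict change, and the article gives reasons for this but no figure.

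Fourth, the type I errors are limiting cases. This also stands. Minimisation balances margins approximately, and the article does not say how age enters. If age is banded, variation within bands is not balanced.

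A reader might also infer that patients of one hospital share testers, which would strengthen the case for a hospital term. The article does not say who performs the tests, so that argument is not used.

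**Conclusion.** The point holds as a conditional loss of precision. The stated two-factor model names none of the four minimisation factors, and the multilevel model leaves its levels and covariates open. If the factors explain 5% to 20% of the variance of the analysed response, the nominal 5% test runs at about 4.4% to 2.8%, and about 1 to 5 points of power are forgone. If they explain none, nothing is lost. These figures rest on an assumed R², full balance, and 0.40 SD on the scale of the analysed response.

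Two stronger readings are tempting, and the documents support neither.

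- *The trial is underpowered because of this.* The sample size was computed without adjustment, and unadjusted power at 100 per group is at least 80.7% at every R² in the table. Only surplus power is forgone.
- *The omission threatens false-positive findings, or the loss is certain.* The error runs in the conservative direction, and its size depends on a quantity that the documents do not give.

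**What to change.** State in Statistical analyses that the between-group models for the primary outcomes, and for secondary outcomes measured in all three arms, include:

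- age as a continuous variable, primary diagnosis and trastuzumab use, each with its interaction with visit where the outcome is repeated;
- treating hospital, as a random intercept or with small hospitals pooled.

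State the levels and covariates of the multilevel regression in the same place. Adjust for the baseline value only where baseline is not also one of the repeated responses. Compliance and satisfaction are assessed only in the two intervention groups, so they fall outside this statement.

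The cost is small: a few more model terms and slightly more analysis work, with no new data, since all four factors are known at allocation. Hospital needs some care, because 360 / (12 × 3) gives an average of only 10 patients per arm per hospital before attrition. That is why a random intercept or pooling is preferable to twelve separate fixed effects crossed with visit. A classical repeated-measures multivariate analysis of variance has no place for a random hospital intercept. Choosing one therefore means fitting the comparison as a mixed model; pooled hospitals can enter the existing model as a fixed factor.

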### Interventions

Patients are randomized to one of three study groups: Onco-Move, OnTrack, or usual care. The Onco-Move program aims at preserving cardiorespiratory fitness, as advocated by Mock [25]. The OnTrack program combines exercise for both cardiorespiratory fitness and muscle strength, as advocated by Courneya [15]. Both the Onco-Move and OnTrack program start in the week of the first cycle of chemotherapy and continue until three weeks after the last cycle of chemotherapy. At the end of chemotherapy all patients receive a leaflet providing encouragement and information on ways to be active.

